### Data management

Survey data will be collected using a secure data collection platform on password-protected tablets and uploaded to a secure, encrypted server accessible only to authorised team members. Qualitative data will be stored on the encrypted server, and audio files will be deleted once transcription and verification are complete. Individuals and families will receive unique identification codes linking responses across time points. A master code sheet linking names to study IDs will be stored separately on a password-protected server, accessible only to core research team members. De-identified data will be stored securely, with statistical code and anonymised data made publicly available following institutional guidelines.

### Statistical analysis

#### Effectiveness analyses

Trial results will be reported following the updated recommendations of the Consolidated Standards of Reporting Trials (CONSORT) 2017 statement for randomised trials of nonpharmacologic treatments (Boutron et al., 2017). All analyses will use an intent-to-treat approach, including all randomised participants regardless of intervention adherence. Statistical significance will be evaluated with a significance level of *p* < 0.05 for each step, with analyses proceeding regardless of preceding step results to fully understand intervention mechanisms.

*Primary effectiveness analyses* will test dual outcome hypotheses sequentially to examine intervention effects on upstream and downstream outcomes using hierarchical linear modelling to account for the nested data structure: (1) repeated measurements within individuals; (2) multiple individuals nested within families; and (3) families randomised to intervention or control conditions. T2 is the primary time point for evaluating intervention effects using group × time interactions, accounting for individual-level fixed effects (*e.g.*, age, gender and baseline measures) and random effects at the individual and family levels (*e.g.*, variation in stress over time).

*Secondary exploratory analyses* will test moderation effects and employ latent growth curve modelling to investigate treatment response patterns and mechanisms of change. Sub-group analyses will examine differential effects by facilitator characteristics, module completion and family and individual characteristics, including time since displacement. Sensitivity analyses will include per-protocol analyses limited to participants completing sufficient dosage of core sessions and alternative missing data approaches.

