## Abstract

Forced displacement heightens mental health risks for children, including psychological, environmental and economic stressors, yet few interventions address whole-family needs within humanitarian contexts. Family-systemic approaches show promise, but evidence on interventions addressing social determinants of mental health remains limited. We will conduct a single-masked, two-arm randomised controlled trial with 550 families in East Amman, Jordan, to evaluate StrongerTogether, a modular whole-family intervention with a financial literacy component. Families experiencing multiple psychosocial challenges will be randomised 1:1 to receive the intervention or enhanced treatment as usual. The trial employs sequential dual outcomes testing, evaluating effectiveness through: (1) upstream improvements in at least one of three primary outcomes (family functioning, parenting practices and caregiver mental health) and (2) direct improvements in adolescent mental health among those with elevated baseline distress. We will also evaluate two implementation tools: ReachNow for family case detection and FamilyACT for facilitator competency assessment. A mixed-methods process evaluation will examine implementation, effectiveness and potential sustainability of core and optional modules. This will be the first rigorous evaluation of an integrated whole-family intervention addressing social and environmental determinants of mental health in humanitarian settings. Findings will inform evidence-based approaches to family mental health support and contribute validated tools for implementation at scale.

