#### Primary effectiveness hypotheses

StrongerTogether will demonstrate effectiveness through sequential testing of dual pathways:H1 (upstream mechanisms): Families receiving StrongerTogether will show significantly greater improvements in at least one upstream determinant (family functioning, parenting practices or caregiver mental health) compared to enhanced treatment as usual (ETAU) families at endline (T2).H2 (direct effects in high-need families): Among families with adolescents showing elevated baseline distress (emotional and/or behavioural difficulties), the intervention will demonstrate superior effectiveness in reducing adolescent distress compared to ETAU at endline (T2).H3 (moderation effect on downstream outcome): The intervention will strengthen the protective relationship between upstream improvements and adolescent mental health, such that treatment families demonstrate greater child mental health benefits from upstream improvements in family functioning, parenting practices or caregiver mental health compared to control families at endline (T2) and follow-up (T3).

The study is fully powered to test H1 (power = 0.85). H2 and H3 are positioned as exploratory analyses, given limitations regarding sample size (see below for sample size calculation).

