### Trial design

The study is a single masked, two-arm RCT with an embedded qualitative process evaluation. Families will be randomised to the intervention or ETAU arms in a 1:1 allocation ratio. Outcomes will be assessed at baseline prior to randomisation (T0), at midline after the completion of core sessions (T1), at endline after the completion of advanced modules (T2, primary time point) and at follow-up 6 months after endline (T3).

The trial employs a sequential, dual outcomes approach to establish effectiveness through multiple pathways comparing treatment *versus* control conditions: (1) upstream improvements in family functioning, parenting practices or caregiver mental health in the full sample; (2) direct improvements in mental health in high-distress adolescents; or (3) enhanced protective effects of upstream improvements on adolescent mental health. Secondary exploratory analyses will examine mechanisms of change over time and the additive effect of the optional modules compared to core modules.

The embedded process evaluation will evaluate implementation, effectiveness and potential sustainability of core and optional modules through mixed methods, including surveys, programme monitoring, staff debrief meetings and qualitative interviews and focus groups. Qualitative activities will be conducted post-intervention (T2) with families who complete and drop out of the intervention, facilitators, outreach staff and other key personnel.

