## Discussion

This study aims to demonstrate the impact of an integrated approach to family mental health support for displaced and vulnerable families. It tests both upstream family mechanisms and direct impacts on adolescent mental health, providing evidence for family-systemic intervention pathways. The results will contribute to the evidence base on whole-family mental health interventions in humanitarian settings, an area currently characterised by substantial gaps, despite promising findings from caregiver-focused programmes (Giusto et al., 2025). Such integrated approaches could promote sustainability and scale in humanitarian and low-resource settings (Troup et al., 2021).

Study strengths include rigorous evidence on interventions addressing social determinants of mental health through inclusion of both displaced and host populations, use of non-specialist facilitators following task-sharing approaches (Raviola et al., 2019; Cohen and Yaeger, 2021) and modular design tailoring to family-specific needs (Kazdin, 2019).

Limitations include the complexity of measuring change in multiple outcomes over time through the sequential dual outcomes approach. While our sample size provides adequate power for testing H1 (upstream mechanisms), we acknowledge that H2 and H3 are positioned as exploratory analyses. Findings from these exploratory analyses will inform future adequately powered mechanistic studies. Additionally, while the intervention addresses multiple family stressors, some structural challenges facing refugee populations will lie beyond the intervention’s scope. Finally, we will use caregiver-report of child mental health challenges for the screening, as this is most feasible in real-world settings. While this approach has been validated in other Arabic-speaking populations (Ababneh and Alomari, 2016; Emam et al., 2016), adult proxy-report of the SDQ could result in underreporting of internalising symptoms compared to adolescent self-report. Nonetheless, adolescent-report SDQ will serve as the primary, upstream effectiveness outcome and both adolescent- and caregiver-report SDQ will be measured at all time points. Research assistants are also trained to report observations and disclosures of severe mental health and protection concerns as part of consent, screening and all rounds of data collection, ensuring referral to specialist support for respondents and their families.

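### H1, the one powered hypothesis, is met if any of three primary outcomes is significant, and the article applies 5% without a split, so the chance of a false H1 claim is up to about 14%, not 5%.

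*Protocol article*

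**What the plan says.** Under Primary effectiveness hypotheses, H1 reads: "Families receiving StrongerTogether will show significantly greater improvements in at least one upstream determinant" at endline (T2). Table 3 names the three primary upstream measures: adolescent-report SCORE-15, the caregiver-report parenting scale and the caregiver-report K10. The Abstract gives the same one-of-three rule.

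The Effectiveness analyses section sets the level at p < 0.05 "for each step, with analyses proceeding regardless of preceding step results to fully understand intervention mechanisms". The Sample size section uses a two-tailed 5% level and 0.85 power for any of the three outcomes, with 220 per group and d = 0.15. Neither section divides the 5% or names a multiplicity procedure.

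The status of H2 and H3 varies by section:

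- The Trial design section describes a "sequential, dual outcomes approach to establish effectiveness through multiple pathways". After the upstream route, its list continues: "2) direct improvements in mental health in high-distress adolescents; or (3) enhanced protective effects of upstream improvements on adolescent mental health".
- The hypotheses section puts H1 to H3 under a heading that calls them primary, then states that only H1 is fully powered and that H2 and H3 are exploratory.
- The Discussion repeats the exploratory label.

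**The concern.** A rule that is met by any one of three significant results gives chance three opportunities. If each test is judged at 5%, the rule as a whole is not a 5% rule. Calling the testing sequential does not help. A sequence controls error only when failure at one step blocks the claims that follow, and here nothing is blocked. In any case, the order runs between H1, H2 and H3, whereas the excess arises inside H1.

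The primary effectiveness claim rests on H1, and the findings are meant to inform use at scale. If the decision rule is settled only after results are known, the claim loses credibility. The second matter is that a reader cannot tell whether a significant H2 or H3, with H1 negative, would be reported as effectiveness.

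**Working it through.** **Inputs.** From the article: three H1 outcomes; success on at least one; 5% two-tailed with no split; 220 per group; d = 0.15; power 0.85; 20% attrition. Not in the article, so assumed: the correlation between the three test statistics (range 0 to 0.9) and the baseline–endline correlation.

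**The plan's own figures.** The article states no family-wise error rate, so there is none to reproduce. The attrition step reproduces: 440 / (1 − 0.20) = 550. The 440 does not follow from the usual two-group formula: n per arm = 2 × [(1.960 + 1.036) / 0.15]² ≈ 799. At that power, 220 per arm corresponds to d = (1.960 + 1.036) × √(2/220) = 0.286, or to d = 0.15 only with a baseline correlation near 0.85, which is not stated. That is a separate matter, but it bears on restating the power.

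**False H1 claim with no effect on any outcome.** If independent: 1 − (1 − 0.05)³ = 1 − 0.8574 = 14.3%. With equally correlated normal test statistics, by numerical integration:

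| Correlation | Unadjusted, 0.05 each | Each at 0.05/3 |
|---|---|---|
| 0 | 14.3% | 4.9% |
| 0.3 | 13.6% | 4.8% |
| 0.5 | 12.5% | 4.5% |
| 0.7 | 10.9% | 3.9% |
| 0.9 | 8.4% | 3.0% |

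Simulation with a million draws agrees to within 0.1 percentage point (12.6% at 0.5). Holm's first step is at 0.05/3, so when all three nulls are true its error rate is the right-hand column.

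**Power cost.** Assume a baseline correlation of 0.5, so that the variance is multiplied by 1 − 0.25 = 0.75, and independent outcomes. The expected z is 0.15 × √(220/2) / √0.75 = 1.817.

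- At 0.05 (critical value 1.960), power is 0.443 per outcome. At least one: 1 − 0.557³ = 0.83.
- At 0.05/3 (critical value 2.394), power is 0.282 per outcome. At least one: 1 − 0.718³ = 0.63.

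**Gating H2.** Suppose H2 were tested at the full 5% after any single Holm rejection. If one upstream effect is real and strong and the other two and H2 are null, Holm tests the remaining two starting at 0.05/2 = 0.025. With independence the error is 1 − 0.975² × 0.95 = 9.7%. Passing the full 5% to H2 is therefore safe only once all three upstream outcomes have been rejected.

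**The case against.** **The level is set per step, not per outcome.** H1 is one step with three outcomes, so the wording could mean 5% for H1 as a whole, with the method left to an analysis plan that is not shown. The article indeed never says that each outcome gets 5%. But the Sample size section applies the undivided 5% to any of the three, and no within-step rule appears. The success rule and the level are both fixed in print, and followed as written they give more than 5%. If a family-wise 5% is meant, one sentence settles it, though the sample size would still not reflect it.

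**14% is a ceiling.** This stands. The outcomes come from the same families and two are caregiver-reported, so some correlation is likely. The rate still exceeds 5% throughout the range shown.

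**A larger overall rate.** A reader might add H2 and H3 as further routes and infer 18.5% for four independent tests, or 40% for ten. The documents do not support these as the trial's error rate. H2 and H3 are twice called exploratory, and running exploratory analyses regardless of H1 is ordinary practice. Ten independent tests is also unrealistic: the H3 tests share one outcome in the same adolescents and reuse the upstream variables. What remains is a conflict of wording between the exploratory label and both the primary heading and the Trial design list.

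**Other apparent contradictions.** The Abstract joins two routes with an and, but it lists what is evaluated and sets no both-must-succeed rule. The Discussion says that "adolescent-report SDQ will serve as the primary, upstream effectiveness outcome". Table 3 and the outcome headings place that measure downstream, so this is a clerical slip that changes no test.

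**Conclusion.** The point holds for H1. As written, the chance of declaring an upstream benefit when there is none is about 11% to 14% for correlations from 0.7 down to 0, with 14.3% the independence ceiling. The correlation range is an assumption, as is the reading, natural but not explicit, that each outcome is tested at 5%. This is a stated rule with the wrong error rate, not a detail missing from a condensed article.

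For H2 and H3 the conclusion is limited to inconsistency. The sections must be reconciled on whether either can establish effectiveness. If the exploratory label governs, the confirmatory error is the H1 figure alone.

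**What to change.** 1. **Primary effectiveness hypotheses and Effectiveness analyses:** claim H1 only for those upstream outcomes that survive Holm at a family-wise two-sided 5% across the three at T2. Hochberg is an alternative, but it needs an assumption about the dependence between tests that Holm does not.
2. **Trial design:** state that H2 and H3 are estimated whatever H1 shows but support no effectiveness claim, and align the heading over H1 to H3. If a confirmatory H2 claim is wanted, pass the full 5% to it only after all three upstream outcomes have been rejected.
3. **Sample size:** restate the power for the adjusted rule, with the baseline correlation and any other assumption behind 440 given explicitly.
4. **Discussion:** correct the word upstream for the adolescent SDQ when the text is next edited.

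The text changes are small and should be made before outcome data are seen. The real cost is power. Under the assumptions in the working, at-least-one power falls from about 83% to 63%. To keep the same per-outcome power by sample size alone would take about 31% more families (799 to 1047 per arm by the plain formula at d = 0.15). At 220 per arm, the effect detectable with 85% power on a single outcome rises from 0.286 to 0.327 without baseline adjustment.

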### Intervention and control conditions

#### Whole-family intervention: StrongerTogether

Intervention characteristics are reported in accordance with the template for intervention description and replication (TIDieR) checklist (Hoffmann et al., 2014). StrongerTogether is a modular, whole-family intervention addressing multiple interconnected family challenges simultaneously. It is positioned as a Level 3 intervention on the IASC MHPSS pyramid,^1^ providing focused, non-specialised mental health support for individual families with psychological distress (IASC, 2007). Non-specialised services rely on task-sharing, an evidence-based approach involving the delivery of mental health services by trained providers who do not have specialised or formal mental health training, improving accessibility (Kazdin, 2019; Raviola et al., 2019).

For each family, the intervention is delivered to at least one caregiver and all adolescents aged between 10 and 17 years. It comprises seven core sessions (including six content-specific sessions and a collaborative ‘transition’ session) addressing family roles, communication, problem-solving and future planning, followed by four optional modules of up to four sessions each covering parenting, caregiver mental health, disagreements and financial literacy, as needed. Session content is manualized, a detailed overview of which can be found in Table 1. Sessions take place weekly at a community centre and are delivered by one non-specialist facilitator face-to-face with individual families, with the support of an assistant to coordinate logistics and provide activities for younger children who may attend but not engage in the entire session. Each session involves a 90-min guided activity or discussion with the entire family, followed by a 30-min discussion with caregivers alone to consolidate the information and support them in their role to implement the strategies. To facilitate home practice and sharing of content with non-attending family members, session content is summarised and provided to families through simple, illustrated handouts and audio-recordings created by the StrongerTogether master trainer to accommodate varying literacy levels.

**Table 1. tab1:** Module content and aims

Central family intervention module		Number of sessions
Module	Aims	

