#### Enhanced treatment as usual (ETAU)

The control condition will be an ETAU consisting of one 30–45 min session comprising a structured, family psychoeducation session delivered by a non-specialist facilitator to the participating caregivers and index adolescent. The scripted session consists of (1) sharing the screening results with the family; (2) discussing common and simple self-care strategies to manage distress; and (3) providing information about available MHPSS, caregiving and financial literacy resources and services. The ETAU will be delivered by non-specialist facilitators, who are different from the StrongerTogether facilitators and who receive a separate 1-day training on the delivery of the psychoeducation session.

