#### Sample size

The sample size calculation was powered for the sequential dual outcomes approach. Assuming a statistical significance level of 5% with an intra-cluster correlation coefficient of 0.02 and a two-tailed test with 0.85 power, a total sample of 440 index adolescents and 440 caregivers is required (220 per group) to detect a minimum effect size of *d* = 0.15 for any of the three upstream primary outcomes (family functioning, parenting practices or caregiver mental health) (Brown et al., 2022, 2024). This is based on conservative estimates consistent with our previous trials with similar populations (Brown et al., 2022) and the feasibility study (Brown et al., 2024). To account for an anticipated 20% attrition rate due to contextual challenges frequently encountered in humanitarian settings, as well as sub-analyses based on family composition and uptake of advanced modules, the study will aim to recruit between 550–600 index adolescents and their families.^2^

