##### Screening

Screening assessments will be administered to caregivers by trained research assistants using tablets in private locations, with family members assessed one-by-one. The screening protocol will assess families for: caregiver mental health challenges (Kessler-10 [K10] ≥ 20); child mental health challenges (Strengths and Difficulties Questionnaire [SDQ] caregiver report ≥17); family relationship challenges (screening questions developed for study); caregiver parenting challenges (screening questions developed for study); financial stress (screening item developed for study); and absence of risks. One caregiver will be asked to report on children in the household. In households with more than three children, they will be asked to report on the children with the most severe emotional and behavioural challenges. Based on the caregiver-reported screening assessment for child mental health challenges, one index adolescent will be selected for subsequent data collection. If more than one child aged 10–17 years scores above the cutoff on the SDQ (≥17), the highest scorer will be selected as the index adolescent for the purposes of the study. Families who meet eligibility requirements will proceed to complete the baseline assessment. More details on the screening protocol, including cut-offs, can be found in Table 2 and Supplementary Document A.

**Table 2. tab2:** Screening protocol for study eligibility

Criterion	Inclusion criteria	Contextual validity
1a. Caregiver mental health	At least one caregiver scores ≥20 on the K10	Cut-off validated for detecting serious mental illness in general populations (Kessler et al., 2003) and feasibility study (⍺ = 0.85) (Brown et al., 2024)
1b. Child mental health challenges	At least one child scores ≥17 on the caregiver-report SDQ	Cut-off validated for detecting serious emotional and behavioural problems in general populations and acceptable internal consistency (⍺ = 0.73) in Arabic versions of parent- and teacher-report (Ababneh and Alomari, 2016; Emam et al., 2016; Al-Hendawi, 2023)
1c. Family relationship challenges	Structured screening questions were developed for this study and piloted in the feasibility study, assessing the presence of significant family conflict or dysfunction causing distress or impairment	Developed for context and validated in a feasibility study

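### The primary model has no facilitator term and the planning ICC of 0.02 names no cluster, so the treatment-effect standard error is too small if facilitators differ

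*Protocol article*

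**What the plan says.** All of this is in the protocol article; a separate analysis plan was not available.

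- **Model (Effectiveness analyses).** Hierarchical linear modelling is to reflect three numbered layers: repeated measurements within a person, then "2) multiple individuals nested within families; and (3) families randomised to intervention or control conditions". Random terms are given for person and family. Facilitator characteristics appear only among the exploratory subgroup analyses and in the process evaluation (Table 4).
- **Planning (Sample size).** The calculation is made "with an intra-cluster correlation coefficient of 0.02 and a two-tailed test with 0.85 power", and states that "a total sample of 440 index adolescents and 440 caregivers is required (220 per group"). The unit to which the ICC belongs is not given.
- **Delivery, intervention arm (Whole-family intervention: StrongerTogether).** Weekly sessions, seven core plus optional modules, are "delivered by one non-specialist facilitator face-to-face with individual families".
- **Delivery, control arm (Enhanced treatment as usual).** One session of 30 to 45 minutes, by facilitators "who are different from the StrongerTogether facilitators".
- **Respondents.** Under Screening, "one index adolescent will be selected for subsequent data collection". Under Data collection, one or more caregivers per family are surveyed. In Table 3 each primary outcome has one type of reporter: the adolescent for SCORE-15 and SDQ, the caregiver for parenting and K10.

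**The concern.** The third layer in the list is the arm. That is the fixed comparison of interest, not a source of correlated errors. The layer that could produce correlation above the family is the facilitator, and it is absent. The design is partially nested: in the intervention arm a family has repeated contact with a facilitator who also sees other families, whereas a control family has one brief contact with someone else. If some facilitators achieve more than others, families who share a facilitator have correlated outcomes. A model with only person and family terms then treats them as independent.

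The planning assumption does not settle the matter, because the ICC of 0.02 has no stated unit. What is at stake is the width of the intervals and the type I error of each of the three upstream tests under H1, where one success is enough.

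There is also a smaller specification problem. For adolescent-reported outcomes there is one respondent per family, so a person intercept and a family intercept describe the same thing and cannot be estimated separately.

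**Working it through.** **Plan's own figures.** The attrition step reproduces: 440 / (1 − 0.20) = 550. The 220 per group does not. For d = 0.15, two-sided 5% and power 0.85, n per arm = 2 × (1.960 + 1.036)² / 0.15² ≈ 799 before any ICC is applied. That is a separate matter. It is relevant here only because the cluster behind the ICC cannot be recovered by working back from the sample size.

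**What the ICC can mean.** The design effect is DE = 1 + (m − 1) × ICC, with m the cluster size.
- Family, one reporter per outcome (as 440 adolescents and 440 caregivers imply): m = 1, DE = 1. The ICC does nothing.
- Family, two caregivers analysed: m = 2, DE = 1.02.
- Facilitator: m is the caseload, and the model has no term for it.

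**Size if facilitators differ.** Inputs from the protocol: 220 analysed intervention families, 220 control families, ICC 0.02. Assumptions: the ICC applies at facilitator level in the intervention arm only, on the scale of the T2 comparison; each family has one facilitator; there are F facilitators with equal caseloads, m = 220/F. F is not stated. I take 10 to 30 as the main range and show 6 as a more extreme case.

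The variance of the difference is proportional to DE + 1 (intervention plus control), whereas the model uses 2. So:
- ratio of true to model SE = √[(DE + 1)/2]
- type I error of the nominal 5% test = 2 × [1 − Φ(1.96 / ratio)]

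Worked for F = 10: m = 22; DE = 1 + 21 × 0.02 = 1.42; ratio = √(2.42/2) = 1.10; 1.96/1.10 = 1.78; type I error 7.5%.

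| F | m | DE | SE ratio | Type I error | Simulated |
|---|---|---|---|---|---|
| 6 | 36.7 | 1.71 | 1.165 | about 9% | 9.1% |
| 10 | 22.0 | 1.42 | 1.10 | 7.5% | 7.7% |
| 15 | 14.7 | 1.27 | 1.07 | 6.6% | 6.8% |
| 20 | 11.0 | 1.20 | 1.05 | 6.2% | 6.4% |
| 30 | 7.3 | 1.13 | 1.03 | 5.7% | 5.5% |

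The simulations used whole-number caseloads (for example 14 for F = 15 and 7 for F = 30).

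The SE ratio is the excess of the true SE over the model SE. Expressed as understatement, 1 − 1/ratio, it is 14% (F = 6), 9% (10), 5% (20) and 3% (30).

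**Sensitivity to the ICC, F from 10 to 30.** At ICC 0.01 the type I error is 6.2% to 5.4%; at ICC 0.05 it is 11.3% to 6.9%.

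**Power.** At 220 per arm, the effect with 85% power without clustering is d = 2.996 × √(2/220) = 0.286. With facilitator ICC 0.02, power for that effect is Φ(2.996/ratio − 1.96): 78% at F = 10 and 83% at F = 30.

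**The case against.** The protocol gives neither the number of facilitators nor their caseload. It fixes one facilitator per session but does not say that a family keeps the same one throughout. Nor does it say that 0.02 is a facilitator ICC. All three points stand, so the figures above are conditional. That facilitators see several families each is still a reasonable inference: about 275 families (half of 550) enter the intervention arm, and facilitators need 10 days of training and weekly group supervision.

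Families are individually randomised, so if the intervention changed nothing for any family, the comparison would remain valid. This also stands. The inflation needs facilitators who truly differ in effect while averaging to zero. Away from that null, the same variation still makes the intervals too narrow for inference beyond these particular facilitators, and the article aims at implementation at scale.

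Degrees-of-freedom methods and fine detail of random effects are commonly left to an analysis plan. That is fair for the details, but this article lists the layers and the random terms, and facilitator is not among them.

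Three stronger readings are tempting and are not supported:
- **Centre as a second missing cluster.** Under Study setting, both organisations deliver both conditions. Centre is therefore not shown to be nested in arm, and omitting it does not by itself make the SE too small.
- **A family intercept that is redundant throughout.** This is certain only for adolescent-reported outcomes. One or more caregivers may be surveyed, so a family effect can be estimated for parenting and K10 if two caregivers in a family are analysed.
- **An invalid analysis of facilitator characteristics.** The article does not say that this analysis crosses arms, so no flaw can be read from it.

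**Conclusion.** The point holds in conditional form. The stated primary model has no term for the facilitator, although delivery makes clustering by facilitator plausible in the intervention arm, and the planning ICC either has no effect or has no counterpart in the model. If facilitators differ in effect, the treatment-effect SE is too small.

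The size is modest under the assumptions made: at ICC 0.02 with 10 to 30 facilitators, the true SE is about 1.10 to 1.03 times the model SE and the type I error about 7.5% to 5.7%. A reader might infer a rate of 9% at the trial's own ICC. That needs as few as 6 facilitators and an ICC of 0.02 at facilitator level, and the protocol states neither. The direction is consistent, towards intervals that are too narrow, and the correction is cheap enough to make before the analysis is fixed.

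**What to change.** 1. State which cluster the ICC of 0.02 refers to.
2. Record facilitator ID for every family and session, and state the number of facilitators and the planned caseload.
3. Fit the primary comparison as a partially nested model: a facilitator random effect in the intervention arm, with ETAU families as singletons or grouped by ETAU facilitator, and small-sample degrees of freedom (Satterthwaite or Kenward-Roger). If families change facilitator, use the main facilitator or a multiple-membership term.
4. For the adolescent-reported outcomes, drop the separate family intercept and keep one intercept per respondent. For caregiver outcomes, keep a family intercept only where more than one caregiver per family is analysed.

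The cost is one recorded identifier, one added model term, slightly wider intervals and a small loss of power. If the facilitator variance is near zero, the result will be close to that of the model as now stated.
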